### Exploratory outcomes

- Proportion of patients achieving reperfusion ( $>90\%$  and  $>50\%$ ) at 24 hours post stroke
- Infarct growth at 24 hours.
  - Proportion of patients achieving recanalisation at 24 hours post stroke

## 12.3 Sample size

An estimated total sample size of 740 patients (equally distributed between two study arms) will yield 80% power to detect an absolute difference of at least 10% in proportion of patients achieving the primary outcome between two arms using two-sided statistical significance threshold of  $p=0.05$ . The estimates in the 'current best practice' group are based on the outcomes of the EXTEND trial where the proportions of LVO patients with the primary outcome (3-month mRS 0-1) were: placebo arm 25%, alteplase arm 28%, with the more conservative assumed proportion taken as 28%. The treatment effect of tenecteplase was based upon the pooled analysis of phase II tenecteplase LVO data where the tenecteplase treatment effect size was 19% greater than alteplase. A more conservative treatment effect of 10% has been assumed for ETERNAL.

Adaptive increase in sample size is planned if the result of interim analysis using data from the first 592 patients are promising, as per the methodology of Mehta and Pocock. The maximum sample size is capped at 1000 patients (500 per arm)..

## **12.4 Interim/Safety analysis**

Two safety parameters (deaths and symptomatic hemorrhages within 36 hours of intervention) will be monitored by the Independent Data Safety Monitoring Committee (DSMC) after each 100 patients have been enrolled. If there are concerns about the safety of participants, DSMC will make a recommendation to the trial steering committee about continuing, stopping, or modifying the trial. To compare the safety of current best practice therapy versus IV tenecteplase, two safety parameters - mortality at three months and the incidence of symptomatic ICH within 36 hours of intervention, will be tested independently. The Haybittle-Peto procedure for generating early stopping boundaries will be used. A recommendation of early termination due to safety reasons will be considered by the DSMC if the corresponding Haybittle-Peto boundary ( $p=0.001$ ,  $Z=3$ ) at a given interim analysis is crossed.

No interim analyses for the primary outcome are planned apart from the analysis for the purposes of adaptive sample size re-estimation as per the “promising zone” methodology of Mehta and Pocock based on the data from the first 592 patients.

## **12.5 Statistical analysis**

The analysis will be conducted following intention-to-treat principles. All outcomes and analyses are prospectively categorized as primary, secondary or exploratory. Differences in all endpoints between the 2 arms of the study will be tested independently at the two-tailed 0.05 level of significance. All estimates of treatment effects will be presented with 95% confidence intervals. No formal adjustments will be undertaken to constrain the overall type I error associated with the secondary and exploratory analyses. Their purpose is to supplement evidence from the primary analysis to more fully characterise the treatment effect. Results from the secondary analyses will be interpreted in this context. Descriptive statistics will be generated for each of the measures used in study.

The primary outcome will be analysed using modified Poisson regression with modified Rankin Scale (mRS) 0-1 (no disability) or return to pre-morbid mRS at 3 months as the dependent variable, treatment arm as an independent variable, and age, baseline NIHSS score, and randomisation-to-groin puncture time (categorized as no EVT, <2 hours, and >2 hours) as treatment covariates. Treatment effect will be presented as adjusted Risk Ratio with corresponding 95% confidence interval (95%CI).

The analyses of dichotomous secondary efficacy and safety outcomes will be conducted using modified Poisson regression with achieving the respective outcome as the dependent variable, treatment arm as an independent variable, and age, baseline NIHSS score, and randomisation-to-groin puncture time (categorized as no EVT, <2 hours, and >2 hours) as treatment covariates. Treatment effects will be presented as adjusted Risk Ratios with corresponding 95% confidence interval (95%CI).

Protocol Number: UOM2102

Protocol Title: ETERNAL LVO

For the ordinal analysis of the day 90 mRS, an ordinal logistic regression analysis model or an assumption-free Generalized OR model analysis will be undertaken on the full range (0-6) of the scale depending on whether the proportional odds assumption is satisfied.

Exploratory outcome analyses will be carried out according to standard statistical principles for comparison of parametric or non-parametric distributions as appropriate.

The details of the statistical analysis will be summarized in a separate Statistical Analysis Plan prior to the lock of the trial data.

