Thus, it is now time to definitively assess tenecteplase in LVO patients in both the early (0-4.5 hours) and delayed (4.5 – 24 hour) time window. ETERNAL LVO will be a phase III trial of treatment with 0.25mg/kg tenecteplase compared to 'standard of care' in patients with a large vessel occlusion and target mismatch on CTP between up to 24 hours after symptom onset. Following publication of our EXTEND trial results we expect there will be some variation in the standard of care for patients with target mismatch in the late time window and anticipate that some clinicians will now wish to give alteplase. However, given that the EXTEND results, as a single trial, may not be sufficient to generate a strong guideline recommendation regarding administration of thrombolysis beyond 4.5 hours, we expect variation in clinical practice in terms of whether 'standard of care' for LVO patients beyond 4.5 hours includes IV alteplase or no thrombolytic. To accommodate this expected variation in practice, the 'standard of care arm' will allow either 0.9mg/kg alteplase or no lytic at the local investigator's discretion, but with the control group treatment pre-specified by the investigator (i.e. alteplase or not) prior to randomisation (covariate adjusted randomisation to minimise imbalances in key prognostic covariates between treatment groups). For example, investigators may be more likely to choose no lytic in patients with larger ischaemic cores (due to perceived risk of ICH), or in those treated in the later part of the 24 hour time window. If not adjusted for at randomisation, this might lead to an imbalance for these variables between the tenecteplase and 'standard of care' groups.

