### 4. Study Design

The study will be a prospective, randomised, open-label, blinded endpoint (PROBE), phase 3, parallel group, superiority trial with covariate-adjusted 1:1 randomisation, and adaptive sample size re-estimation in ischemic stroke patients with large vessel occlusion presenting to hospital within 24 hours of symptom onset (or last known well within 24 hours). Patients will be randomised to treatment with either standard of care (no intravenous thrombolytic treatment or intravenous alteplase 0.9mg/kg at the investigators discretion) or intravenous tenecteplase (0.25mg/kg). A covariate-adjusted randomisation procedure will be used to minimise imbalances for the following covariates: clinician intention to treat with alteplase or no thrombolysis if randomised to standard of care arm, age, NIHSS, premorbid mRS, site of Large Vessel Occlusion (Intracranial ICA and M1 vs extracranial ICA and M2, with tandem ICA occlusions to be considered intracranial for the purpose of covariate adjustment), and onset-to-randomisation time (less than 4.5h, 4.5-12h and 12-24h, where wake-up stroke/uncertain onset is 'last seen well within last 24 hours').

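### The primary model leaves out four of the six factors used to balance randomisation, which makes the test mildly conservative

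*Protocol*

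**What the plan says.** The synopsis and sections 4, 7.1 and 8.4 describe the same covariate-adjusted allocation. Section 4 balances on "clinician intention to treat with alteplase or no thrombolysis if randomised to standard of care arm, age, NIHSS, premorbid mRS, site of Large Vessel Occlusion" and, sixth, onset-to-randomisation time in three bins.

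The first factor exists because the control arm is mixed. The Background says that it "will allow either 0.9mg/kg alteplase or no lytic at the local" investigator's discretion, with the choice declared before randomisation. The Background and section 8.1 describe the balanced factors as prognostic and expect the choice of control to depend on core size and lateness.

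Section 12.5 then fixes the primary model: modified Poisson regression with "treatment arm as an independent variable, and age, baseline NIHSS score" and randomisation-to-groin-puncture time in three categories, one of which is no thrombectomy. The list is repeated for the dichotomous secondary and safety outcomes. The synopsis gives age, NIHSS and an onset-to-puncture time. Further detail is deferred to a statistical analysis plan, which is not at hand, but the protocol itself closes the covariate list.

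**The concern.** Balancing the arms on a prognostic factor removes most of that factor's contribution to the chance variation of the treatment contrast. A model without the factor does not know this. It leaves the factor's variance in the residual, so the standard error overstates the real spread of the estimate. Intervals come out too wide, the test rejects too rarely under the null, and some power is given away compared with a model that contains the balancing factors.

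Two omissions stand out. Premorbid mRS sets the threshold for success, because a patient with premorbid mRS 2 succeeds by returning to 2. Intended control treatment is expected, on the protocol's own reasoning, to track core size and lateness. Puncture time does not replace onset-to-randomisation time: in section 12.5 its clock starts at randomisation.

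**Working it through.** **1. The two lists side by side**

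| Factor | Balanced at randomisation | In primary model (12.5) |
|---|---|---|
| Intended control treatment | yes | no |
| Age | yes | yes |
| NIHSS | yes | yes |
| Premorbid mRS | yes | no |
| Occlusion site | yes | no |
| Onset-to-randomisation time | yes | no |
| Randomisation-to-groin-puncture time | no | yes (post-randomisation) |

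Four of six are absent. The synopsis model omits the same four.

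**2. The plan's own figure**

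Inputs from sections 12.3 and 12.5: 740 in total, allocated 1:1 and so 370 in each arm; a design that "will yield 80% power to detect an absolute difference of at least 10% in proportion of patients achieving the primary outcome"; control rate from "placebo arm 25%, alteplase arm 28%, with the more conservative assumed proportion taken as 28"%; effect from "A more conservative treatment effect of 10% has been assumed for ETERNAL"; endpoints "tested independently at the two-tailed 0.05 level of significance". The comparison is thus 28% against 38%, with mean rate 0.33.

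- Uncorrected: n per arm = [1.96·√(2·0.33·0.67) + 0.842·√(0.28·0.72 + 0.38·0.62)]² / 0.10² = 346, or 692 in total.
- Continuity-corrected: (346/4)·[1 + √(1 + 4/(346·0.10))]² = 366 per arm, or 732 in total.

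The stated 740 is reproduced by the corrected formula. At 370 per arm, power is about 80.4% with the correction and 82.6% without it. No covariates enter this calculation.

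**3. Normal approximation**

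Let r be the share of outcome variance explained by the omitted, balanced factors. The true spread is then √(1−r) times the reported standard error. The standard error of the risk difference is √((0.2016 + 0.2356)/370) = 0.0344, so the expected z is 0.10/0.0344 = 2.91. With s = √(1−r):

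- type I error with the factors omitted: 2·[1 − Φ(1.96/s)]
- power with the factors omitted: 1 − Φ((1.96 − 2.91)/s)
- power with the factors included: 1 − Φ(1.96 − 2.91/s)
- interval width ratio: 1/s

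| r (assumed) | Type I error, omitted | Power, omitted | Power, included | Intervals wider by |
|---|---|---|---|---|
| 2% | 4.8% | 83.1% | 83.6% | 1% |
| 5% | 4.4% | 83.5% | 84.7% | 3% |
| 10% | 3.9% | 84.1% | 86.6% | 5% |
| 20% | 2.8% | 85.6% | 90.2% | 12% |

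**4. Simulation**

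Each scenario used 4,000 trials of 740 patients, minimisation on six factors with a biased coin of 0.8, and modified Poisson regression with robust standard errors. Both models were fitted to the same trials, and puncture time was in neither. The prognostic effects are assumptions. In the moderate case, on the log-odds scale, they are: intended alteplase +0.4; premorbid mRS 1 and 2, −0.5 and −0.7; occlusion site 0.5; the two later time bins −0.3 and −0.5. Weak is half of these and strong is double. Age and NIHSS carry −0.5 and −0.7 per standard deviation throughout.

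| Assumed effects | Type I error: two factors / six | Power: two factors / six | Power difference (points) | Mean SE under the null: two / six | Ratio |
|---|---|---|---|---|---|
| Weak | 4.5% / 4.6% | 87.1% / 87.5% | 0.4 | 0.1116 / 0.1109 | 1.01 |
| Moderate | 4.7% / 5.1% | 87.2% / 87.8% | 0.7 | 0.1121 / 0.1097 | 1.02 |
| Strong | 3.7% / 5.4% | 87.8% / 90.6% | 2.8 | 0.1130 / 0.1054 | 1.07 |

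Power differences are taken before rounding. In the strong case under the null, the two-factor estimate had an actual spread of 0.1055 against a mean reported standard error of 0.1130, which is the mechanism at work. Monte Carlo error is about 0.3 points for type I error and 0.5 points for power, so the weak and moderate rows show little difference in either.

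**The case against.** The strongest reply is that the harm is small and in the safe direction. That stands. The omission does not raise type I error, the 80% in section 12.3 was computed without covariates, and the two-factor model kept about 87% power in every simulated scenario. A reader might infer from the word conservative that the trial falls short of its planned power. The documents do not support that: the loss is relative to a fuller model, not to the plan.

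It is also fair that neither calculation measures the loss for the exact model specified. Puncture category may be related to occlusion site and onset time and absorb part of their prognostic value. Likewise, the endpoint already credits return to baseline at premorbid mRS 2, which may weaken what premorbid mRS still predicts. Both points could reduce the loss. Neither removes the mismatch.

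A reader might also infer that the plan is at fault for not showing whether benefit differs between an alteplase control and a no-lytic control. That is a separate question. A main effect for intended control would not answer it. An interaction or subgroup analysis would, and such analyses are commonly left to the analysis plan.

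Deferral to the analysis plan does not answer the core point, because the protocol fixes the covariate list and a plan with a different list would contradict it.

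**Conclusion.** The concern holds as a modest inefficiency and an internal mismatch, not as a threat to validity. The count of four omitted factors and the direction of the effect are firm. The size is not in the documents. Over the assumed weak-to-strong range, with puncture time left out of both models, intervals are about 1% to 7% wider and power is about 0.4 to 2.8 points lower than with all six factors. If the omitted factors explained 20% of outcome variance, the normal approximation would give 12% and 4.6 points. If they predict little, almost nothing is lost. The change is worth making because it costs almost nothing, not because the primary result would otherwise be unsafe.

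**What to change.** In section 12.5 and the synopsis, add intended control treatment, premorbid mRS, occlusion site and onset-to-randomisation time bin to age and NIHSS in the primary model. Use the same set in the dichotomous secondary and safety models where event counts allow, and align the adjustment sentence in section 12.2.

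In the same edit, state explicitly how randomisation-to-groin-puncture time is handled. It is measured after randomisation and includes a no-thrombectomy category, so whether it stays in the primary model, moves to a supplementary analysis or is removed should be decided openly and not happen as a side effect of rewriting the list. The synopsis and section 12.5 also start its clock at different points and need to agree.

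The cost is wording only: all four variables are already recorded for randomisation. The change should be made before anyone sees unblinded outcome data, and so before the sample-size re-estimation at 592 patients.

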| Study sample size and statistical considerations: | 
An estimated total sample size of 740 patients (equally distributed between two study arms) will yield 80% power to detect an absolute difference of at least 10% in proportion of patients achieving the primary outcome between two arms using two-sided statistical significance threshold of <math>p=0.05</math>. The estimates in the 'current best practice' group are based on the outcomes of the EXTEND trial where the proportions of LVO patients with the primary outcome (3-month mRS 0-1) were: placebo arm 25%, alteplase arm 28%, with the more conservative assumed proportion taken as 28%. The treatment effect of tenecteplase was based upon the pooled analysis of phase II tenecteplase LVO data where the tenecteplase treatment effect size was 19% greater than alteplase. A more conservative treatment effect of 10% has been assumed for ETERNAL.
 
Adaptive increase in sample size is planned if the result of interim analysis using data from the first 592 patients are promising, as per the methodology of Mehta and Pocock. The maximum sample size is capped at 1000 patients (500 per arm).
 
The primary analysis will be conducted on intention to treat basis. A detailed statistical analysis plan will be formulated before the database lock. The analysis of the primary outcome will be conducted using a modified Poisson regression with excellent functional outcome (mRS 0-1) or return to the pre-morbid mRS as the dependent variable, treatment group as the independent variable and age, NIHSS and onset-to-ECR puncture time (categorized as no ECR, <2 hours, and > 2 hours) as treatment covariates. Secondary and exploratory analyses will be undertaken using appropriate regression models.
 |

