## 2. Background

Ischaemic stroke is the leading cause of adult disability in the world. The current standard of care for treatment of patients with acute ischaemic stroke is intravenous recombinant tissue plasminogen activator (tPA, or alteplase), although its use currently remains restricted to less than 4.5 hours from symptom onset. Presently, only 13% of ischaemic stroke patients in Australia receive alteplase, partly due to the time window restriction. Additionally, alteplase performs relatively poorly in patients with a large vessel occlusion (LVO). Despite availability of alteplase, stroke patients with LVO face a devastating outcome due to the large area of brain tissue affected, resulting in >50% of patients dead or highly disabled at 3 months. However, recent trials have shown that endovascular clot retrieval or thrombectomy (EVT) results in at least a doubling of the odds of disability-free survival, compared to treatment with alteplase alone. It is therefore no surprise that there has been worldwide enthusiasm to translate EVT into routine practice. However, endovascular thrombectomy requires considerable operator expertise and infrastructure, so is limited to high volume stroke centres (which also ensures lower complication rates). This means there are inevitable delays in LVO patients receiving EVT, particularly in rural and regional centres, but also in large cities where inter-hospital transfers can be slow. Intravenous thrombolysis given prior to transfer to a thrombectomy capable centre ('drip and ship') may lead to vessel recanalisation in transit and negate the need for thrombectomy. However, alteplase only leads to recanalization prior to thrombectomy in 10% of patients. Further, its use is currently restricted to <4.5 hours after symptom onset.

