## Reperfusion at 24hr with 0.25 mg/kg TNK

[figure not shown]

The benefit of identifying ischemic tissue and salvageable tissue prior to reperfusion therapy and by excluding mimics using CTP was highlighted by a subsequent phase II tenecteplase trial (ATTEST), which enrolled patients via standard clinical criteria. ATTEST was negative for the primary outcome. Although ATTEST did not use CTP to select patients, fortunately, CTP was still performed. When the ATTEST data was pooled with our Australian TNK trial, only 34% of ATTEST patients had salvageable tissue meeting 'target mismatch' criteria on CTP (explaining the differing results). In the pooled data, there was a substantial clinical benefit over alteplase in patients treated with tenecteplase who had salvageable tissue (return to all usual activities [mRS 0-1] occurred in 35% tenecteplase vs 22% alteplase-treated patients), *with a lower brain haemorrhage rate*.

The recent EXTEND-IA TNK trial, also by our group, showed that 0.25mg/kg tenecteplase was more effective than the standard stroke thrombolytic drug alteplase in patients treated up to 4.5 hours from symptom onset at opening large vessel occlusions prior to thrombectomy in patients who met target mismatch criteria on CTP. The primary outcome of reperfusion at the initial angiogram occurred in 22% of tenecteplase versus 10% of alteplase patients ( $p=0.02$ ). Thus, *1 in 5 LVO patients treated with tenecteplase did not require subsequent thrombectomy* and the number needed to treat with tenecteplase rather than alteplase to prevent one thrombectomy was nine. Although all patients with persisting LVO still went on to thrombectomy, tenecteplase was also associated with improved functional outcome at 90 days (common odds ratio 1.7, 95%CI 1.0-2.8,  $p=0.037$ , Figure 3). This emphasises the benefits of earlier reperfusion with tenecteplase.

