### Safety

- Proportion of patients with symptomatic intra-cerebral haemorrhage (sICH) defined as: parenchymal haematoma type 2 (PH2) within 36 hours of treatment combined with neurological deterioration leading to an increase of  $\geq 4$  points on the NIHSS from baseline, or the lowest NIHSS value between baseline and 24 hours
- Proportion of patients with death due to any cause
- Proportion of patients with Modified Rankin Scale (mRS) 5-6 at 3 months (severe disability or death).

All secondary and safety outcomes will also be analysed adjusted for: age, NIHSS, randomisation time to groin puncture time in bins, including a bin for no EVT performed

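### The only stated primary model adjusts for thrombectomy use and puncture time, which are settled after randomisation, so its risk ratio does not in general estimate the intention-to-treat effect

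*Protocol*

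**What the plan says.** Section 12.5 states "The analysis will be conducted following intention-to-treat principles". It then gives one primary analysis, a modified Poisson regression of the day-90 outcome on treatment, age, baseline NIHSS and "randomisation-to-groin puncture time (categorized as no EVT, <2 hours, and >2 hours) as treatment covariates", reported as an adjusted risk ratio. No unadjusted or baseline-only primary analysis is stated. The same covariates are set for the dichotomous secondary efficacy and safety outcomes.

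The synopsis describes the same model with a different variable: "NIHSS and onset-to-ECR puncture time", also in three categories with one for no procedure. Under Safety, section 12.2 says that secondary and safety outcomes will also be analysed adjusted for age, NIHSS and "randomisation time to groin puncture time in bins, including a bin for no EVT performed".

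Three other statements bear on this:
- The synopsis allows thrombectomy but does not require it, and section 8.5 makes treatment open-label.
- The Background says that lysis before transfer "may lead to vessel recanalisation in transit and negate the need for thrombectomy".
- The Background cites reperfusion at the initial angiogram of 22% with tenecteplase and 10% with alteplase, and says that "1 in 5 LVO patients treated with tenecteplase did not require subsequent thrombectomy".

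**The concern.** A clock that starts at randomisation cannot measure a baseline characteristic. Starting it at onset, as the synopsis does, does not help, because the puncture that stops it still follows allocation. Clinicians decide on thrombectomy knowing the allocated treatment. On the protocol's own premises, tenecteplase moves some patients with good prospects into the no-EVT category.

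Two things follow. First, the covariate lies on the path from treatment to outcome, so holding it constant sets aside whatever benefit runs through early reperfusion. Secondly, within the no-EVT category the arms are no longer comparable. That category mixes patients who reperfused early with patients who had no thrombectomy for other reasons, in proportions that treatment has altered.

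At stake is what the primary result means. The objective in section 3 is superiority of a strategy of giving tenecteplase. The reported ratio would instead be a comparison conditional on later care. Among the secondary outcomes, TICI 2b/3 on the first angiographic run is especially awkward, because that finding helps to determine whether thrombectomy follows. An early haemorrhage or death could likewise affect whether a patient is punctured, so the sICH and mortality comparisons could be distorted.

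**Working it through.** **The plan's own figure.** Section 12.3 takes 28% versus 38%, two-sided 0.05, 80% power and 740 patients. The usual two-proportion formula gives 346 per arm (692) without continuity correction and 366 per arm (732) with it. At 370 per arm, power is 82.6% or 80.5% respectively. The sample size is sound for the intention-to-treat contrast, a risk ratio of 38/28 = 1.357.

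**Inputs from the protocol.** Outcome 28% versus 38%; early reperfusion 10% versus 22%; 1:1 allocation.

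**Assumptions (not in the protocol).**
- 65% of early reperfusers have an excellent outcome.
- A share *q* of the non-reperfused, equal in both arms, has no thrombectomy, and those patients do half as well as the ones who have it.
- Puncture timing does not differ by arm, so the two timed bins act as one.

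**Implied rates.** Control non-reperfused: (0.28 − 0.10 × 0.65)/0.90 = 0.239. There are two ways to reach 38% with tenecteplase:
- (a) Reperfusers stay at 65%. Non-reperfused: (0.38 − 0.22 × 0.65)/0.78 = 0.304.
- (b) All rates rise by one factor: k = 0.38/(0.22 × 0.65 + 0.78 × 0.239) = 1.154, which takes reperfusers to 75%.

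**What the model estimates in large samples.** With stratum weights w₀ and w₁ for control and tenecteplase, and S the stratum's events over both arms, the fitted RR solves

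Σ S · w₁RR/(w₀ + w₁RR) = tenecteplase events.

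*Extreme case: all reperfusers coded no EVT, all others treated (q = 0).*
- No EVT: w = 0.10 and 0.22, S = 0.065 + 0.143 = 0.208.
- EVT: w = 0.90 and 0.78, S = 0.215 + 0.237 = 0.452.
- Under (a), try RR = 1.19: 0.208 × 0.2618/0.3618 + 0.452 × 0.9282/1.8282 = 0.151 + 0.229 = 0.380, as required.
- Under (b), both strata have ratio 1.154, so RR = 1.154.
- Share of log RR removed: 1 − ln 1.19/ln 1.357 = 1 − 0.174/0.305 = 43% under (a); 1 − 0.143/0.305 = 53% under (b).

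*Other cases (true RR 1.36).*

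| Early reperfusers | q = 0 | 10% | 20% | 40% |
|---|---|---|---|---|
| All coded no EVT, (b) | 1.15 | 1.26 | 1.31 | 1.35 |
| All coded no EVT, (a) | 1.19 | 1.28 | 1.32 | 1.36 |
| Half have a puncture time, (a) | 1.28 | 1.35 | 1.36 | 1.36 |
| All have a puncture time, (a) | 1.36 | 1.35 | 1.34 | 1.31 |

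**The sign can change.** Assume 60% excellent outcome in reperfusers, half of the others without thrombectomy at 10%, and treated patients at 35% (early puncture) or 30% (late), with no other drug effect. The intention-to-treat ratio is then 1.19 and the adjusted ratio 1.21.

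**Rough translation to power.** At 370 per arm against 28%, using the uncorrected formula, a tenecteplase rate of 33% (RR 1.18) gives 31%, 35% (1.25) gives 54%, 36% (1.29) gives 65% and 38% (1.36) gives 83%.

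**The case against.** The strongest reply accepts that the covariate is post-randomisation but disputes the consequence.

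- **Classification.** The 22% versus 10% was measured at the initial angiogram, so those patients reached the angiography suite and may well have a puncture time. Section 12.5 does not say which bin they enter. If they have one, attenuation in the table is at most slight to moderate.
- **Who lacks thrombectomy.** The extreme case needs every non-reperfused patient to be treated, yet thrombectomy is optional and section 6.4 expects more than half of patients to be drip-and-ship. With 20–40% of the others untreated, most of the attenuation goes.
- **Source of the reperfusion figures.** They come from treatment within 4.5 hours against alteplase. This trial runs to 24 hours, and its control arm may receive no lytic.
- **Safety.** The word *also* in section 12.2 suggests that the adjusted analyses are additional, and section 12.4 has the monitoring committee test death and sICH with no thrombectomy adjustment mentioned.

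All four stand, and they limit what can be claimed. A reader might infer that the benefit will be adjusted away and that power will fall to about 30%; that holds only at the extreme. A reader might also infer that harms will be hidden; the documents support only that the adjusted safety comparisons could be distorted.

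None of this repairs the primary model. A bias whose size and sign depend on coding and access to care is not a defence of it. Nor does a precision argument help: intended control treatment, premorbid mRS, occlusion site and onset-to-randomisation time are balanced at randomisation and available as covariates, yet they are absent from the model.

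**Conclusion.** The covariate choice is wrong as written. That the adjusted risk ratio does not in general estimate the intention-to-treat effect follows from the text alone: thrombectomy is optional and decided after open-label allocation, and the Background expects the drug to alter the need for it.

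The size is not established. Under the stated assumptions, a true ratio of 1.36 becomes anything from about 1.15–1.19 to about 1.36. Attenuation is the likely direction on the protocol's premises, but a slight bias away from the null is possible. The range rests on an assumed 65% outcome in early reperfusers, an assumed halving of outcome in untreated non-reperfusers, and reperfusion rates from an earlier time window.

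Separately, the synopsis and section 12.5 disagree on when the clock starts, and exactly 2 hours falls in no category. With entry allowed up to 24 hours, the under-2-hour bin would be sparse if counted from onset. These are drafting faults and add nothing to the bias argument.

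**What to change.** In the synopsis (statistical considerations), section 12.2 (closing sentence under Safety) and section 12.5, remove puncture time and thrombectomy status from the primary, secondary and safety models. Adjust only for variables fixed before randomisation: age, baseline NIHSS and, if wished, the remaining randomisation covariates (intended control treatment, premorbid mRS, occlusion site, onset-to-randomisation time).

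Report thrombectomy use and puncture time by arm as descriptive process outcomes, or use them in an analysis labelled exploratory or mediation. If any puncture-time analysis is kept, choose one clock start, assign exactly 2 hours to a bin, and state how a patient punctured for angiography but not needing thrombectomy is classified.

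The cost is a protocol amendment, which under section 15.10 needs ethics approval and, if substantial, regulatory approval. No patients or data are added. The change is best made before outcomes by arm are examined at the 592-patient interim analysis.
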